**Fig. 2 Fig2:**
[figure not shown]
Follow-up within 4 weeks of hospital discharge*Profile and role of the transition nurse*

The prerequisite for the TN is to have worked in geriatric units (in acute care or in rehabilitation care facilities). The TN will be trained by the research team in the components and tools of the intervention and in the organisation of primary care. In each participating hospital, the TN will meet the hospital care providers and will establish contact with the local primary care providers who usually take care of the patients at home. Table 1 describes what the TN will do for the intervention patients.

**Table 1 Tab1:** Description of activities of the transition nurse (TN)

Time of the transition	Action of the TN	Main contact	Tool implemented
During the patient’s stay in hospital	Collect data about the patient, his caregiver, his primary care physician, and current primary care providers;	Medical team and social workers of the discharging hospital	Transitional care file intended for the TN: hospital part
	Verify that the admission geriatric assessment has been carried out by the medical team and complete it if necessary;		
	Develop the discharge plan in collaboration with the physicians, nurses, physiotherapists, and social workers of the hospital.		
When the day of hospital discharge is set	Check that the date of returning home is known by the patient, his caregiver, and the primary care physician;	The patient's primary care physician	
	Check that the discharge summary and plan have been transmitted to the primary care physician;		
	Check the organisation of the transport if needed;		
	Check that a primary care physician visit is planned (at home or in office) during the month following discharge;		
	Prepare the handover sheet, which includes the meetings scheduled (medical exams, biological monitoring), the contacts scheduled with the TN (by telephone or home visit), the telephone number and timetable where the TN can be reached, and the contact information of the primary care providers.		
The day of hospital discharge	Check that the prescriptions for the discharge care plan are written (medications, physical therapy, medical equipment, etc.);	Patient and his caregiver	Handover sheet intended for the patient and the primary care providers
	Explain the discharge plan to the patient or his caregiver;		
	Give the completed handover sheet to the patient or caregiver and verify that the visits scheduled are planned in accordance with the patient or caregiver's availability;		
	Check that the discharge plan will be implemented with the social worker;		
	Check that the inpatient nursing care plan, along with the medical discharge summary, is in the handover sheet.		
After hospital discharge: follow-up by home visit and telephone	Verify the effective implementation of human and material aid; ask about difficulties and seek to resolve problems;	Patient and his caregiver Primary care providers Geriatrician	Transitional care file intended for the TN: home part
	Help to prevent the risk of falls by having a look at the environment at home;		
	Ensure good medication compliance; verify the autonomy and clinical status of the patient, and contact stakeholders (nurse, primary care physician, hospital physician) if necessary;		
	Retrieve the results of biological monitoring and of medical visits; answer questions from the patient and his caregiver;		
	Provide regular reports to the primary care providers (by completing the handover sheet) and to the geriatrician.		

### Control period

No intervention liable to affect the care provided for the patients, the organisation of care, or the practices of health care professionals will be implemented during the control period (time steps without intervention). The patients will be discharged according to the usual care plan of each participating hospital. The medical team will proceed as usual to deliver a medical and geriatric assessment of the patients according to existing recommendations. The communication of information to the primary care providers (nurse, primary care physician, etc.) is left to the discretion of the medical teams of the discharging hospitals, according to their existing work habits.

In the control period, the normal care practices will be assessed following the Template for Intervention Description and Replication (TIDieR) guidelines [14].

### Outcomes and measurements

#### Primary outcome

The primary outcome is the 30-day unscheduled hospital readmission or emergency visit rate after the index hospital discharge. Unscheduled hospital readmissions are hospitalisations that are not planned at the time of discharge (for example, hospitalisation through Accidents and Emergency departments or upon the request of the primary care physician). A follow-up at 30 days after discharge evaluates care transition failures, before and after hospital discharge.

#### Secondary outcomes

The secondary outcomes are:

Patient safety and quality issues at home:Survival without hospitalisation after discharge (within 30 days)Mortality rate at 30 days after dischargeQuality of life measured with the French version of the EuroQol EQ-5D-3 L [15] at 30 days after dischargePatients’ satisfaction with the quality of preparation for post-hospital care measured with the Care Transition Measure® questionnaire [16] at 30 days after discharge. The French version of this questionnaire will be validated separately.

Delivery of the intervention:Time period from the decision relative to the date of discharge to the discharge itselfTime period from discharge to the implementation of human and material aids at homeTime period for the communication of relevant information to the primary care providersNumber of contacts between the TN and the primary care providers or the hospital providers after discharge

### Medico-economic study

The medico-economic study has a “piggy-back” design because it is added to the clinical study: the data necessary for the medico-economic study will be obtained from the detailed observation of the resources used for each patient included. Data collection will be done prospectively.

The medico-economic study will have two components.The first component will be a cost-effectiveness analysis of the main criterion assessed in the study. It will provide a cost per unscheduled hospitalisation or emergency visit prevented. The health insurance perspective is chosen. The time limit is 30 days after the index hospital discharge. The costs assessed will be direct medical expenses (hospital expenses, reimbursement of consultations or examinations, etc.), non-medical expenses (reimbursement of transport), and care transition program expenses (time spent by the TN for each patient at the three times of the transition).The second component will be a budgetary impact study of the implementation of the intervention. The time limit is 12 months after the index hospital discharge. Health insurance and societal perspectives will be considered. The costs assessed will be direct and indirect medical expenses (medical and social expenses, family expenses, institutional care expenses, etc.) and care transition program expenses. Various scenarios may be proposed in order to study the financial impact of the care transition program on the funders.

### Sample size calculation

The number of patients has been determined according to a compromise between the inclusion ability of the units and the needed power, using the method of M.A. Hussey and J.P. Hughes [17]. The following hypotheses were used:A 30-day unscheduled hospital readmission or emergency visit rate after discharge of 20 % in the control group [2].A 10 % rate in the intervention group: the absolute risk reduction of the 30-day unscheduled hospital readmission or emergency visit rate ranges from 2.0 to 28.1 points according to previous studies with a bridging intervention based on a transition coach [18–24].A variation coefficient between clusters of 10 %. In cluster randomized trials, the variation coefficient is generally between 0.1 and 0.4. We have chosen a value of 0.1, because the variation of the outcome between units is supposed to be low. Furthermore, M.A. Hussey and J.P. Hughes have shown that, because the stepped wedge design uses both within-cluster and between-cluster information, power is relatively insensitive to variations of the coefficient of variation [17].

Under these hypotheses, for 6 clusters, 7 time periods, and an unilateral alpha risk of 5 %, the inclusion of 14 patients per cluster and per time period allows to reach a power of 70 %. The whole number of patients is 588. To allow for about 10 % missing data on the primary outcome, 15 patients per cluster and per time period will be included, for a total number of 630 patients.

A unilateral test has been chosen as it seems unlikely that exposure to the care transition program will increase the rate of unscheduled hospital readmissions or emergency visits within 30 days: these events are the result of hospital care factors, primary care factors, and patient factors. It does not seem possible for the intervention tested in this study to intensify the effect of these factors. The literature reviews do not report a significant increase in readmission rates associated with interventions on the hospital-to-home transition for older patients [5–8].

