**Methods:**

This is a multicentre, stepped-wedge cluster randomised trial.

The program will be implemented at three times of the transition: 1) during the patient’s stay in hospital: development of a discharge plan, creation of a transitional care file, and notification of the primary care physician about inpatient care and hospital discharge by the transition nurse; 2) on the day of discharge: meeting between the transition nurse and the patient to review the follow-up recommendations; and 3) for 4 weeks after discharge: follow-up by the transition nurse.

The primary outcome is the 30-day unscheduled hospital readmission or emergency visit rate after the index hospital discharge.

The patients enrolled will be aged 75 or older, hospitalized in an acute care geriatric unit, and at risk of hospital readmission or an emergency visit after returning home.

In all, 630 patients will be included over a 14-month period. Data analysis will be blinded to allocation, but due to the nature of the intervention, physicians and patients will not be blinded.

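### Going from 588 to 630 patients covers 6.7 % missing primary outcomes, not the stated allowance of about 10 %

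*Protocol article*

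**What the plan says.** All the figures are in the Protocol article, section Sample size calculation. The design is fixed as "for 6 clusters, 7 time periods, and an unilateral alpha risk of 5" %. The planning rates are "A 30-day unscheduled hospital readmission or emergency visit rate after discharge of 20 % in the control group" and "A 10 % rate in the intervention group", with a between-cluster coefficient of variation of 0.1, and the method is that of Hussey and Hughes.

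On these inputs the article states that "the inclusion of 14 patients per cluster and per time period allows to reach a power of 70" %, and continues: "The whole number of patients is 588". The inflation follows: "To allow for about 10 % missing data on the primary outcome", the plan is that "15 patients per cluster and per time period will be included, for a total number of 630 patients".

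The Methods part of the abstract repeats the final number: "In all, 630 patients will be included over a 14-month period". The article gives no other allowance for missing outcomes.

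**The concern.** An allowance for missing data should leave the number used in the power calculation once the expected losses have occurred. Adding one patient to 14 raises the cell size by 7.1 %, and that extra patient is 6.7 % of the 15 enrolled. Neither figure is 10 %. If outcomes are lost at the rate the plan itself expects, the evaluable number falls below the one behind the power statement.

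The margin matters because the design has little to spare. Planned power is only 70 %, and that already relies on a one-sided 5 % test. The outcome is obtained by telephoning each patient (section Blinding) in an at-risk population aged 75 or older (section Participants), so losses are a realistic prospect. Anyone monitoring the trial against this section would believe that a 10 % loss had been provided for, when the shortfall begins just above 6.7 %.

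**Working it through.** **Inputs**, all from the section Sample size calculation: I = 6 clusters; T = 7 periods; one-sided α = 5 % (z = 1.645); control rate 0.20; intervention rate 0.10; coefficient of variation 0.1; 14 patients per cell before inflation and 15 after; missing outcomes about 10 %.

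**1. The plan's totals.**
- 6 × 7 × 14 = 588, as stated.
- 6 × 7 × 15 = 630, as stated.

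**2. The plan's power.** The Hussey and Hughes variance of the intervention effect is

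Var = I·s²·(s² + T·τ²) / [(I·U − W)·s² + (U² + I·T·U − T·W − I·V)·τ²]

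One cluster crosses over at each step after the first period. Then U (treated cells) = 21, W (sum of squared period totals) = 91 and V (sum of squared cluster totals) = 91. Hence I·U − W = 126 − 91 = 35, and the second bracket is 441 + 882 − 637 − 546 = 140.

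The between-cluster SD is τ = 0.1 × 0.20 = 0.02, so τ² = 0.0004. The article does not state the individual variance. The control-rate value 0.20 × 0.80 = 0.16 is assumed here because it reproduces the stated power.

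At 14 per cell:
- s² = 0.16/14 = 0.011429
- Var = 6 × 0.011429 × (0.011429 + 0.0028) / (35 × 0.011429 + 140 × 0.0004) = 0.000976/0.4560 = 0.002140
- SE = 0.04626
- Power = Φ(0.10/0.04626 − 1.645) = Φ(0.517) = 0.697

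This agrees with the stated 70 %.

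**3. What 630 covers.** The largest missing share that leaves 588 evaluable is 1 − 588/630 = 42/630 = 6.67 %.

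**4. What 10 % missing leaves.** 630 × 0.90 = 567 evaluable, on average 15 × 0.90 = 13.5 per cell. The shortfall is 588 − 567 = 21.

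**5. What 10 % missing would require.** 588/0.90 = 653.3, so 654 patients. Per cell, 14/0.90 = 15.6, so 16 whole patients, or 6 × 7 × 16 = 672 in total.

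**6. Power at 13.5 per cell.**
- s² = 0.16/13.5 = 0.011852
- Var = 6 × 0.011852 × (0.011852 + 0.0028) / (35 × 0.011852 + 0.056) = 0.001042/0.4708 = 0.002213
- SE = 0.04704
- Power = Φ(0.10/0.04704 − 1.645) = Φ(0.481) = 0.685

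| Evaluable per cell | Evaluable in total | Missing share of 630 | Power |
|---|---|---|---|
| 15 | 630 | 0 % | 72.1 % |
| 14 | 588 | 6.7 % | 69.7 % |
| 13.5 | 567 | 10 % | 68.5 % |

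**7. Could another common formula explain 630?** Multiplying by 1.10 gives 588 × 1.10 = 646.8 in total, or 14 × 1.10 = 15.4 per cell. Rounding 15.4 down to 15 is the likely origin of the figure, though the article does not say so. That shortcut does not protect 588 either: 647 × 0.90 = 582.

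**The case against.** The arithmetic is not in dispute; the weight is.

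- **The power effect is very small.** The stated 70 % is itself a rounding of 69.7 %, and the drop to 68.5 % changes no design decision. This stands.
- **Other inputs matter more.** With the variance taken at the mean rate (0.15 × 0.85 = 0.1275), power is 77.5 % at 14 per cell and 76.3 % at 13.5, so it stays above 70 %. At the upper end of the coefficient-of-variation range that the section quotes (0.4, so τ = 0.08), power at 14 per cell falls to 57.5 %. That is a loss of about 12 points, roughly ten times the effect at issue. This stands as a matter of proportion. However, the mean-rate variance does not reproduce the stated 70 %, and neither choice alters the 6.7 %.
- **The text is hedged.** The allowance is given as approximate, and the section presents the sample size as a trade-off between what the units can recruit and the power wanted. So 588 is the size at which the chosen power is reached rather than a strict minimum. Recruitment is also set in whole patients per cell, where 15 covers 6.7 % and 16 covers 1 − 14/16 = 12.5 %; no whole number gives exactly 10 %. This is a fair reason to keep 15 per cell. It does not justify describing 15 as covering about 10 %, since the stated rate is one and a half times the rate covered.
- **The other places are correct.** The 588, and the 630 in the abstract, are right as they stand. The fault is confined to the allowance in one sentence.

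**Conclusion.** The concern holds, as a small arithmetic error. The increase from 588 to 630 absorbs 6.7 % missing primary outcomes, not about 10 %. At 10 % missing, 567 patients are evaluable, 21 below the number behind the power statement. This part rests only on figures printed in the article.

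The power consequence is 69.7 % to 68.5 %, a little over one point. It assumes the control-rate variance, which reproduces the plan's 70 %, equal cell sizes, and missing outcomes spread evenly over clusters and periods. The design and the analysis are unaffected; what needs correcting is the stated missing-data margin.

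**What to change.** Change one sentence in the section Sample size calculation, in one of two ways:

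- keep 15 per cell and 630 in total, and give the allowance as 6.7 % (about 7 %) missing primary outcomes; or
- keep the 10 % expectation and state that it leaves 567 evaluable patients (13.5 per cell on average), with power of about 68 %.

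The second is more informative if 10 % is still the realistic expectation. Stating the individual variance used would let a reader reproduce the power directly.

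Neither option needs extra patients or any change to the total in the abstract. Enrolling 16 per cell (672) would cover 10 % in full, but that means 42 more patients in a trial whose enrolment has already begun (section Trial status) and whose size was limited by recruitment capacity. A gain of about one point of power does not call for it.

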### Blinding

Health care providers delivering the intervention, participants, and researchers will not be blinded to the intervention status. Contamination between clusters will nonetheless be prevented, because it is impossible to implement the care transition program without a TN. Primary outcome measures will be carried out by a clinical research associate who will contact each patient by telephone and who will not be blinded to the participant's status as intervention or control, for practical reasons. Information bias will be minimised, because the primary outcome (the 30-day unscheduled hospital readmission or emergency visit rate) is an objective criterion that does not require interpretation (contrary to clinical events). Data analysis will be blinded to allocation.

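### An unblinded telephone assessment of the primary outcome is defended as needing no interpretation, but the outcome's own definition needs a judgement for some direct admissions, and capture of events could differ by condition

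*Protocol article*

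**What the plan says.** The Blinding section of the protocol article states who measures the primary outcome and how: "Primary outcome measures will be carried out by a clinical research associate who will contact each patient by telephone". This associate is not blinded to the patient's status, for practical reasons. The patients, who are the informants, are not blinded either: "Health care providers delivering the intervention, participants, and researchers will not be blinded to the intervention status". Only the data analysis is blinded. The section holds that information bias will be minimised because the outcome "is an objective criterion that does not require interpretation (contrary to clinical events").

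The Primary outcome section combines unscheduled readmission with emergency visit, within 30 days of the index discharge, and defines the first component: "Unscheduled hospital readmissions are hospitalisations that are not planned at the time of discharge". Two routes follow as examples: "hospitalisation through Accidents and Emergency departments or upon the request of the primary care physician".

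The Medico-economic study section covers the same 30 days: "the data necessary for the medico-economic study will be obtained from the detailed observation of the resources used for each patient included". It does not name the source of those data.

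**The concern.** The article makes a deliberate choice (an unblinded caller) and gives a reason for accepting it (nothing to interpret). The reason conflicts with the definition. Whether a stay was planned at the time of discharge is a fact about the discharge plan, and someone has to establish it when the route of admission does not settle it. Blinding the analysis cannot repair a classification made earlier by someone who knew the condition.

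A second matter affects both components. Events reach the trial through a telephone contact with patients aged 75 or older, some of whom qualify partly through cognitive impairment. Under intervention only, a nurse follows the patient weekly for 4 weeks and prepares a handover sheet listing scheduled meetings. Recall of events, and the evidence of what was planned, could therefore differ between conditions. At stake is a bias in the primary effect estimate, in a trial planned at only 70 % power with a one-sided test.

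**Working it through.** **Where judgement enters.** Setting the definition against the claim that no interpretation is needed:

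- Emergency visit, including a stay that began with one: an event in itself. No judgement on planning.
- Admission at the primary care physician's request: named as an example of unscheduled. Little judgement.
- Any other direct admission: counts only if it was not planned at discharge. Someone must decide, and the Blinding section leaves the measurement to a caller "who will not be blinded to the" patient's status.

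The contradiction is real but confined mainly to the third group. Missed or unreported events can arise in all three.

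**Inputs for the illustration** (Sample size calculation section): 20 % in control, 10 % under intervention, between-cluster coefficient of variation 0.1, 6 clusters, 7 periods, 14 patients per cluster-period, one-sided 5 %. The capture rates below are assumptions; the documents give none.

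**Formula** (Hussey and Hughes, one cluster crossing per step): with I = 6, T = 7, U = 21, W = 91 and V = 91,

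Var = I·s²·(s² + T·t²) / [(I·U − W)·s² + (U² + I·T·U − T·W − I·V)·t²] = 6·s²·(s² + 7·t²) / (35·s² + 140·t²),

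where s² = p₀(1 − p₀)/14, t² = (0.1·p₀)² and p₀ is the control rate. Power = Φ(difference/SE − 1.645).

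**The plan's own figure.** s² = 0.20 × 0.80/14 = 0.011429 and t² = 0.0004, so SE = 0.0463. Then 0.10/0.0463 = 2.162 and power = Φ(0.517) = 69.7 %, which agrees with the stated 70 %.

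**Better capture under intervention (85 % control, 95 % intervention).** Observed rates are 0.20 × 0.85 = 0.170 and 0.10 × 0.95 = 0.095, a difference of 7.5 points. With p₀ = 0.17, SE = 0.0431 and power = Φ(1.739 − 1.645) = 53.7 %.

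**A wider gap (80 % and 95 %).** Observed 0.160 and 0.095, a difference of 6.5 points; SE = 0.0420; power = Φ(1.547 − 1.645) = 46.1 %.

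**Better capture in control (95 % control, 85 % intervention), no true effect at 20 %.** Observed 0.190 and 0.170, a spurious benefit of 2 points; SE = 0.0453; rejection rate = Φ(0.442 − 1.645) = 11.4 % against a nominal 5 %.

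**Better capture under intervention (85 % and 95 %), no true effect.** Observed 0.170 and 0.190, an apparent increase; the one-sided rejection rate is about 1.7 %.

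**Sensitivity to the variance convention.** With the variance taken at the mean observed rate, the starting power is 77.5 %, and the two power figures become 60.6 % and 51.8 %. The levels move; the loss is similar.

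**The case against.** The strongest case on the other side has five parts.

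- **The interpretive gap is narrow.** This stands: emergency visits count in themselves and physician-requested admissions are named. A reader might infer that every stay needs a judgement by the caller; the definition does not support that.
- **The article discloses the unblinded caller and claims only that bias is minimised.** This also stands, and it would be wrong to say that the protocol declares bias impossible. Yet the reason given for the minimisation is the one that fails.
- **Patient recall is not stated to be the only source, and verification may be in the full protocol, which is not shown.** Fair, so the absence of a described check is not the finding. The finding is that the article rests its safeguard on a statement its own definition contradicts.
- **Differential recall is conjecture, and its direction is open.** This stands. Nothing says the caller uses the nurse's file or the handover sheet. Better recall under intervention would work against the programme and cost power; it would not create a false positive. The reverse could arise if an unblinded classifier leaned towards calling stays planned under intervention, but the documents do not show this either. Cognitive impairment is one example within one of six risk criteria, any two of which suffice, so it applies to some patients and not to all.
- **The cost study cannot be assumed to hold hospital records.** This stands. A reader might infer that suitable records are already gathered. The Medico-economic study section names no source, and if the data came from the same telephone call, a check against them would be circular.

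**Conclusion.** The statement that the primary outcome needs no interpretation is wrong for direct admissions other than those through emergency or at the primary care physician's request. It therefore cannot carry the defence of an unblinded telephone assessment. Beyond that, differential capture of events is a risk and not a demonstrated bias: neither its size nor its direction can be fixed from the documents.

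If capture differed by 10 percentage points, the consequence would be either a loss of about 16 points of power (69.7 % to 53.7 %) or a one-sided error of about 11 %, depending on which condition is captured better. These figures rest on assumed capture rates and on the design inputs that reproduce the planned power. The point does not dispute the sample size, and it does not support a claim that the trial's result will be biased in a given direction. It justifies a cheap improvement to how the outcome is recorded and classified.

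**What to change.** 1. Delete or correct the sentence in the Blinding section that the outcome needs no interpretation.
2. Have the associate record only facts for every stay or emergency visit: date, hospital, route of entry, and whether the stay was listed in the discharge plan in the medical file. Use the medical file and not the handover sheet, which exists only under intervention.
3. Classify events as unscheduled by one fixed written rule, identical in both conditions, applied by the data management and analysis centre, whose analysis is already to be blinded to allocation. In a stepped wedge, unit and calendar date together can reveal the condition, so the listing used for classification should omit the unit and give days since discharge instead of dates.
4. Where the 30-day hospital-use data of the cost study come from hospital or insurance records, cross-check the telephone-reported events against them in the same way in both conditions. State the source in the Medico-economic study section. If the source is the telephone call itself, this step gives no independent check.

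Cost: a short amendment and a small amount of extra data-management work, with no additional assessor. The associate can stay unblinded, so the practical reasons given in the article are respected. One limit remains: the nurse helps to develop the discharge plan under intervention, so the plan itself may be more complete there.
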